### 2.4. Experimental Design

A cross-over randomized control trial (RCT) will be adopted to investigate the acute effect of the MSK program for PD on anxiety, selected kinematic and kinetic parameters, and frontal cortex hemodynamic responses during gait initiation and during steady-state walking in people with PD, under the following conditions: (a) a synchronous learning format and (b) an asynchronous remote video-based format.

Volunteers will be asked to attend both conditions in a randomized order, separated by a washing-out period of at least one week. Levels of anxiety, kinematic, and DLPFC hemodynamic activity data will be collected before and after the two different interventions, which will last for approximately 45 min. The control situation will be defined based on the data collection at the same time points as above, but without any intervention following the 1-week washing out period. Ethical approval has been granted by Ethics Committee of University of Thessaly-Protocol number 2007. All procedures will be conducted in accordance with the declaration of Helsinki, in an appropriately equipped and safe laboratory, by qualified researchers with relevant experience. Research data are confidential and available to participants, who will be allowed to stop their participation at any time without previous notice.

### 2.5. Randomization and Blinding

Participants will be randomly (randomizer.org) assigned by a leading researcher blinded to the study either to start with the synchronous intervention or with the asynchronous remote video-based intervention. Two evaluators also blinded to the scope of the study will take all measurements before and after interventions. It will not be possible to blind participants as the delivery of the class will reveal their allocation.

### 2.6. Intervention

All intervention classes, synchronous and asynchronous remote video-based, will be held in the Biomechanics & Ergonomics Laboratory (b) at the Department of Physical Education and Sport Science, University of Thessaly, Trikala, Greece. Their structure is focusing on refining innate musicality and coordination via rhythmic movement, hearing training and improvisation.

Risk management strategy includes a qualified carer who will be present during both the synchronous and asynchronous modalities, full explanation of the experimental procedures, controlled laboratory temperatures at about 22° Celsius, as well as the continuous presence of at least two members of the research team.

The protocol has a duration of 45 min of rhythmic training and includes sections of warming up, stretching, breathing, movement combinations, a dance sequence, and recovery. Each exercise is accompanied by music that provides a clear and predictable rhythm. More specifically, the beat or rhythm of the music is used as a guide for the timing and duration of specific movements, allowing people with PD to coordinate their movements with the music. Simple values will be introduced, such as whole notes, half notes, and quarter notes, clapping and tapping, breathing, and sounds. Class will be accompanied by recorded classical piano music to meet the needs of the synchronous learning format and asynchronous remote video-based format. The intensity of the class will be moderate, at approximately 3 MET. The instructor will be an experienced dance teacher in musicokinetic education. Protocol details can be found in Table 1.

### 2.7. Outcome Measures

Volunteers will attend both conditions (synchronous and asynchronous remote video-based) in a randomized order, separated by a washing-out period of at least a week. Kinematic, DLPFC hemodynamic activity and levels of anxiety data will be collected before (base-line data) and after the two interventions, while, on a third occasion, control data will be collected at the same time points but without any intervention.

Two experienced evaluators blinded to the group allocation will collect data. Baseline data collection will include: (1) Anthropometric characteristics (sex, age, body mass index), H&Y scale; (2) Anxiety Hamilton Rating Scale (Hamilton 1960); (3) Gait analysis using a 10-camera 3D motion analysis system (Vicon T-series, Oxford, UK) and two force platforms (Bertec 4060–10, OH) embedded in the laboratory floor; (4) Frontal cortex hemodynamic responses using f-NIRS (Portalite by Artinis NL); and (5) Unified Parkinson’s Disease Assessment Scale-III (UPDRS-III). Post intervention measurements will include: (1) Anxiety Hamilton Rating Scale (Hamilton 1960); (2) Gait analysis using a 10-camera 3D motion analysis system (Vicon T-series, Oxford, UK) and two force platforms (Bertec 4060–10, OH) embedded in the laboratory floor; (3) Frontal cortex hemodynamic responses using f-NIRS (Portalite by Artinis NL); and (4) Unified Parkinson’s Disease Assessment Scale-III (UPDRS-III).

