The aim of the proposed study is to examine the acute effects of a MSK program on select kinematic and kinetic parameters alongside DLPFC hemodynamics during gait initiation and steady-state walking in individuals with PD, performed in the following conditions: (a) a synchronous learning format and (b) an asynchronous remote video-based format. The program is customized for PD patients without deviating from the objectives of musicokinetic education. Primary outcomes will be the acute effects of a MSK protocol in people with PD on anxiety and locomotion. Secondary outcomes will be the effectiveness of an asynchronous remote video-based format for those patients that are not able to attend classes on site.

The novelty of the current design is the combined implementation of functional near-infrared spectroscopy (f-NIRS) in parallel with 3D gait analysis, which, until now, has yet to be evaluated in Parkinsonian patients following a MSK intervention. f-NIRS is extensively employed in chronic neurological disorders associated with aging, enabling direct measurements of the absolute concentrations of oxygenated and deoxygenated hemoglobin in the brain [16]. In relation to Parkinson’s disease, f-NIRS investigates the activity of the prefrontal cortex during tasks such as gait, postural stability, and dual-task performance, thereby determining motor vs. non-motor effects and executive dysfunction due to the disease’s pathology [16]. We shall non-invasively evaluate DLPFC hemodynamic activity in Brodmann area 46 during gait kinematics and kinetics evaluation using f-NIRS in order to investigate the cognitive involvement. Moreover, we argue that f-NIRS in conjunction with 3D gait analysis may provide valuable insights for understanding the mechanisms underlying the benefits of MSK program for PD.

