### 2.3. Sample Size Calculation

The total sample size was estimated through an a priori power analysis, using the G power V 3.1.9.7 software (Heinrich-Heine-Universität, Düsseldorf, Germany). The following input parameters were applied using a repeated-measure ANOVA design: effect size f = 0.33, α = 0.05, power = 0.80, and correlation between repeated measures r = 0.50. The a priori power calculation revealed that the initial sample size required is 11. By considering a 10% dropout rate, 13 individuals with Parkinson’s disease will be recruited to voluntarily participate in this study.

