### 2.10. Statistical Analyses

The normal distribution of the dataset will be assessed using the Shapiro–Wilk test. Analyses of variance (ANOVAs) with repeated measures will be used to analyze kinematic and kinetic parameters and pre-frontal cortex hemodynamic responses during gait initiation and during the steady state between the two interventions and time points. Significant interactions and main effects will be further examined using Bonferroni post hoc analysis. The significance level will be set at *p* < 0.05.

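### The no-intervention control session lies outside the randomisation, and apparently always comes last, so the MSK-versus-control contrast that the primary aim needs is not a randomised comparison

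*Protocol article*

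**What the plan says.** All references are to the protocol article.

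- **What is randomised.** Section 2.5 assigns participants at random "either to start with the synchronous intervention or with the asynchronous remote video-based intervention". Section 2.7 repeats this: "Volunteers will attend both conditions (synchronous and asynchronous remote video-based) in a randomized order". Under Section 2.4 the two are "separated by a washing-out period of at least one week".
- **Where the control goes.** Section 2.4 defines it as data taken at the same time points, "but without any intervention following the 1-week washing out period". Section 2.7 places it after the description of the two interventions: "while, on a third occasion, control data will be collected at the same time points but without any intervention".
- **What the trial is for.** Section 1, repeated in Section 3: "Primary outcomes will be the acute effects of a MSK protocol in people with PD on anxiety and locomotion". The usefulness of the remote format is the secondary outcome. Section 2.4 calls the design a randomised controlled cross-over.
- **How it will be analysed.** Section 2.10 plans repeated-measures ANOVA "between the two interventions and time points". It names neither a control level nor a period term.

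**The concern.** Both active conditions are MSK, and Section 3 expects them to work equally well. Comparing them cannot show that MSK has an acute effect; only the comparison with the no-intervention session can. Yet no participant can start with control, and on the natural reading the only sequences are synchronous-asynchronous-control (S-A-C) and asynchronous-synchronous-control (A-S-C).

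Measurements are taken before and after each session, so a constant shift in level from one visit to the next cancels in the change score. Two things do not cancel:

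- **A visit effect on the pre-post change itself.** Examples are growing familiarity with the laboratory, the gait trials and the f-NIRS equipment, or with repeated Hamilton ratings. Familiarity accumulates towards the last visit, which is the control.
- **Carryover.** The control would follow two MSK sessions in every participant.

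Either could enlarge or shrink the apparent effect of MSK. A larger sample would not remove such a bias.

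**Working it through.** **1. The plan's own figure.** Section 2.3 gives "effect size f = 0.33, α = 0.05, power = 0.80, and correlation between repeated measures r = 0.50" and a required sample of 11, raised to 13 for 10% dropout. The number of repeated measures, m, is not stated. For a within-subject F test in one group with sphericity, λ = N·m·f²/(1−r), with df (m−1) and (N−1)(m−1).

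- With m = 6 and N = 11, λ = 11 × 6 × 0.33²/0.50 = 14.37 and power is 0.802, so 11 is reproduced.
- With m = 2, 3, 4 or 5 the required N would be 21, 17, 14 or 13.
- Dropout: 11/0.90 = 12.2, rounded up to 13.

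Six measures is what three sessions with two time points give. That is consistent with the control having been counted as a third condition, though the article does not say so.

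**2. Can the contrast be separated from the visit?** Model the within-session change on sequence, visit and condition.

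| Sequences | Visit effect | Rank / columns | MSK − control estimable? |
|---|---|---|---|
| S-A-C, A-S-C | unrestricted | 5 / 6 | No |
| S-A-C, A-S-C | linear | 5 / 5 | Yes, only if drift is linear |
| All six orders | unrestricted | 10 / 10 | Yes |

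In the first row, synchronous minus asynchronous is still estimable.

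The price of assuming linearity, per participant, with unit change SD and uncorrelated changes:

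- Unadjusted contrast, (Y₁+Y₂)/2 − Y₃: variance 1/2 + 1 = 1.5.
- Slope estimate, Y₂ − Y₁, with formats balanced over visits 1 and 2: variance 2, uncorrelated with the unadjusted contrast.
- Adjusted contrast: variance 1.5 + 1.5² × 2 = 6.
- Standard error ratio: √(6/1.5) = 2.

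**3. Illustration of size.** The documents give no drift value, so τ = 0.1, 0.2 and 0.3 SD of the change score is an assumption. With r = 0.50 among all measures, the SD of a change is √(2 × (1 − 0.50)) = 1 measurement SD, and changes in different sessions are uncorrelated. There is no true MSK effect, and the test is a two-sided 5% paired t test of mean MSK change against control change.

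- Linear drift: MSK sits at mean visit 1.5 and control at visit 3, so the size of the bias is (3 − 1.5)τ = 1.5τ, that is 0.15, 0.30 or 0.45 SD.
- Only visit 1 differs, by τ: each participant has one of two MSK sessions there, so the bias is 0.5τ, that is 0.05, 0.10 or 0.15 SD.
- Noncentrality is bias × √n / SD of the contrast. For linear τ = 0.2 and n = 13: 0.30 × √13/√1.5 = 0.883.
- If session changes instead correlate at 0.5, the contrast variance is (1 + 0.5)/2 + 1 − 2 × 0.5 = 0.75.

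| Drift shape | Correlation of changes | n | τ = 0.1 | τ = 0.2 | τ = 0.3 |
|---|---|---|---|---|---|
| Linear | 0 | 13 | 0.069 | 0.129 | 0.230 |
| Linear | 0 | 11 | 0.066 | 0.114 | 0.197 |
| Linear | 0.5 | 13 | 0.089 | 0.210 | 0.407 |
| Visit 1 only | 0 | 13 | 0.052 | 0.058 | 0.069 |

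Entries are rejection rates; the nominal rate is 0.05. With all six orders used equally, each condition has mean visit 2 and the linear-drift bias is 0.

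**The case against.** - **A third occasion may mean only a third separate visit.** The wording allows this, and Section 2.4 does not say which washout precedes the control. The last position is therefore the apparent reading, not an explicit one. That the control is not randomised does not depend on it: Section 2.5 lets participants start only with one of the two formats.
- **Pre-measures in each session protect the comparison.** They do against constant level shifts, but not against a changing pre-post response or carryover.
- **The drift is hypothetical.** It is. If familiarisation is mostly over after the first visit, the inflation is small. The figures show what could happen, not what will.
- **A model could adjust for it.** A reader might infer that no analysis can separate control from visit. That goes too far. A linear drift is estimable because the formats are randomised over visits 1 and 2. The adjustment rests on an assumption that the design cannot check and doubles the standard error.
- **Blinding.** A reader might also infer that the evaluators would recognise the control visit by its position. Sections 2.5 and 2.7 describe them as blinded to the scope of the study and to allocation, and nothing says that they know the visit schedule.
- **The whole trial is compromised.** It is not. Synchronous versus asynchronous is randomised, and it is the between-condition comparison that Section 2.10 names.

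**Conclusion.** The point holds for MSK versus control. That this contrast is not randomised follows directly from Sections 2.4, 2.5 and 2.7, and it matters because the primary aim depends on it in a trial presented as randomised and controlled. That the control is always last is the likelier reading. On that reading the contrast is aliased with any unrestricted third-visit effect.

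The direction and size of the bias cannot be known from the documents. Across the scenarios tabulated for 13 completers, the false-positive rate runs from 0.052 to 0.407, depending on the assumed amount and shape of drift and on the correlation between session changes. Confidence is high on the missing randomisation and low on any particular figure for the bias.

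This should be settled before the first visit, because later analysis can repair it only by assuming a drift shape.

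**What to change.** - **Sections 2.4, 2.5 and 2.7:** randomise the order of all three sessions (synchronous, asynchronous, control) over the six possible sequences, with two participants per sequence (6 × 2 = 12) and the 13th assigned at random to one of them. Keep the existing gap of at least one week between every pair of sessions. Replace the wording on which format comes first and on the third occasion.
- **Section 2.10:** include control as a third condition and add a period term.
- **If visits have already started:** report MSK versus control as a non-randomised comparison.

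The cost is a new randomisation list and a short amendment. Visits, participants and measurements stay the same, and the sample size of 11 (13 with dropout) is not altered by the change of order.

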### 2.8. Primary Outcome Measures

Levels of anxiety will be evaluated via Hamilton Anxiety Rating Scale [17]. Ground reaction force (GRF) data captured at 1000 Hz for the right and left leg by the force platforms will be synchronized with the kinematic data obtained by the Vicon motion analysis system at 100 Hz. Twenty reflective markers will be placed bilaterally on the pelvis and lower extremities according to the marker set described in the literature [18,19]. The symmetrical center of rotation estimation (SCoRE) [20] and the symmetrical axes of rotation approach (SARA) [21] will be applied to estimate the hip joint center and the knee joint flexion axis, respectively.

For evaluation of DLPFC activation during gait, non-invasive measurements of local cortical hemoglobin (hBT) (i.e., blood volume), deoxyhemoglobin (HbH), and oxyhemoglobin (HbT) will be executed using a portable spectrometer (f-NIRS: PortaLite mini, Artinis Medical Systems, Zetten, Netherlands) with a capacity of light emission and detection of 840–760 nm, using a sampling frequency of 10 hz. The distance between NIRS optodes (i.e., sender and receiver) will be 25 mm, enabling a maximum penetration depth of 23 mm and an average measurement depth of 12.5 mm. Increased brain activity is generally considered to mirror increases in local HbO_2_ and decreases in HHb, resting on the mechanistic foundation of neurovascular coupling [22]. Decreased HbO_2_ responses can be considered a measure of neuronal suppression or altered hemodynamic re-distribution. The f-NIRS probe will be placed on the PFC of the right DLPFC [23]. To suppress any confounding influence of light, the probe shall be covered using black tape and a black cloth. For the collection, storage and visualization of f-NIRS data, the software application Oxysoft (Artinis Medical Systems, Zetten, The Netherlands) will be used. In addition to computing relative measurements of HBo2, HHb, and HbT using the modified Lambert Beer law, exportation of raw f-NIRS data will be performed and analyzed using a custom (MATLAB) script, used to inspect data for artifacts and processing.

Gait initiation (self-triggered) will be tested 3 times with each leg placed on a separate force platform according to the methodology employed in previous studies. Subsequently, the participants will walk barefoot along the 10 m laboratory walkway within ±5% of their preferred walking speed [24,25]. Trials will be repeated until at least 3 complete gait cycles are recorded with each foot making a clean contact on the force platforms located in the middle of the walkway.

### 2.9. Secondary Outcome Measures

Demographic and anthropometric measurements: age, sex, body mass index, marital status, educational level, profession, duration of the disease, medication and symptomatology. According to the WHO protocol (2016), body mass index (BMI) is classified as follows: thin (BMI < 18.5); eutrophic (BMI 18.5–24.9); overweight (BMI 25.0–29.9); pre-obesity and obesity (BMI > 30.0).

Unified Parkinson’s Disease Assessment Scale-III (UPDRS-III): The maximum value indicates greater involvement of the disease and the minimum normality. The UPDRS-III is a reliable (r-0.96) and valid scale.

The effectiveness of the synchronous learning format vs. the asynchronous remote video-based format will be based on the results of the aforementioned measurements and the response of patients who complete the protocol.

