## 3. Expected Results

The aim of the proposed study is to examine the acute effects of a MSK program on anxiety levels and select kinematic and kinetic parameters alongside DLPFC hemodynamics during gait initiation and steady-state walking in individuals with PD, performed in the following conditions: (a) synchronous learning format and (b) asynchronous remote video-based format. The program is customized for PD patients without deviating from the objectives of musicokinetic education. Primary outcomes will be the acute effects of a MSK protocol in people with PD on anxiety and locomotion. Secondary outcomes will be the effectiveness of asynchronous remote video-based format for those patients that are not able to attend classes on site. To our knowledge, this is the first time that MSK program will be introduced in PD as a form of exercise. Since motor dysfunctions are associated with anxiety [2], rhythmic-based interventions can potentially improve or even regulate it.

Anxiety may be a result of the neurochemical changes of the disease itself or a psychological reaction to the stress of the disease, and can be seen in various manifestations such as phobia, generalized anxiety disorder, or panic attacks [3,26]. The rationale behind the use of the purpose-designed MSK program for PD is its effectiveness in addressing the primordial motor expression of humans. Guidance by the rules of music, where periodicity is distinct, may eventually be beneficial in “calibrating” the brain, reducing motor difficulties, restoring movement harmony, and, thus, reducing anxiety. Moreover, we expect that the combined influence of improved rhythmicity, potentially improving the automatization of motor control, would be reflected in decreased DLPFC activation due to reduced executive load in the planned control of movements.

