Given that recent research on rhythmic training has yielded beneficial results using methods such as rhythmic auditory stimulation (RAS) or dance, which includes rhythm as a key component, it is expected that the said MSK program will be an effective non-pharmacological intervention in dealing with PD-derived gait impairments. Finally, it is expected that both means, synchronous on site and tele format, will be equally effective in regulating the aforementioned biopsychological parameters as the content of the class and teaching styles will be the same. Research on the use of remote dance programs for people with PD has indicated acceptable feasibility and significant improvements in depression and quality of life, but at the same time has underlined the importance of live dance [27,28].

In general, patients with PD frequently experience disruptions in the 24 h daily profile of both behavioral and biological markers [29]. This lack of rhythmicity or disruption of inner-rhythm can negatively affect elements of health [30,31] and physical performance [32]. Therefore, it is rather prudent to establish non-pharmacological strategies able to reduce the global impact of the disease and improve the quality of life of both patients and the patient’s caregiver.

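### The secondary question is whether the video class works for people who cannot attend, but the only contrast named for it is live versus video, and the no-intervention control is assigned to no contrast

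*Protocol article*

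**What the plan says.** The Introduction sets the secondary question: "Secondary outcomes will be the effectiveness of an asynchronous remote video-based format for those patients that are not able to attend classes on site". Section 3 (Expected Results) repeats it in nearly the same words.

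Section 2.9 says how that effectiveness will be judged: "The effectiveness of the synchronous learning format vs. the asynchronous remote video-based format will be based on the results of the aforementioned measurements", together with the response of those who complete the protocol. The only pair it names is live against video.

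The design also has a no-intervention condition. Section 2.4: "The control situation will be defined based on the data collection at the same time points as above, but without any intervention". Section 2.7 adds that "on a third occasion, control data will be collected at the same time points but without any intervention".

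Section 2.10 describes repeated-measures ANOVAs for gait initiation and "during the steady state between the two interventions and time points", with Bonferroni post hoc tests. It does not mention the control occasion.

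Section 3 states the expected result: "it is expected that both means, synchronous on site and tele format, will be equally effective".

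**The concern.** The question and the contrast do not match. Someone who cannot reach the class does not have the live class as an option. The article does not say what that person's alternative is, but the natural reading is no class, and the trial collects a no-class condition. The contrast that is named compares the video with the option these patients lack.

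The named contrast can mislead in two ways. If the difference is close to zero, as section 3 expects, the data cannot tell two effective formats from two ineffective ones. If the video helps but less than the live class, the difference favours the live class, although the video may still be better than nothing. What is at stake is whether the trial can support any statement about the video format on its own.

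**Working it through.** **1. The passages side by side**

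| Element | Where | What is compared |
|---|---|---|
| Secondary question | Introduction; section 3 | Effect of the video format for people unable to attend |
| How it is judged | 2.9 | Live vs video, plus response of completers |
| Analysis | 2.10 | Two interventions × time points |
| Control data | 2.4, 2.7 | Same people and time points, no intervention; no contrast named |

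No section names video versus control.

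**2. What the named contrast can show**

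Let L, V and C be the true mean pre-to-post changes in the live, video and control conditions. The effect of the video relative to no class is V − C. The named contrast is L − V = (L − C) − (V − C). If L − V = 0, then V − C equals L − C, and that common value may be zero or anything else. L − V therefore carries no information on V − C unless L − C is also estimated, and that needs the control.

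The time factor in section 2.10 does give V itself. But V includes whatever changes between two measurements without a class, such as repeat testing. The control occasion is what would remove that, so the within-video change helps only in part.

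**3. The plan's own sample size**

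Section 2.3 gives "effect size f = 0.33, α = 0.05, power = 0.80, and correlation between repeated measures r = 0.50" and arrives at 11, then 13 after 10% dropout. It does not state the number of measurements m. For one group, with sphericity assumed, λ = f²·N·m/(1 − r), df1 = m − 1 and df2 = (N − 1)(m − 1).

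| m | Smallest N for 80% power |
|---|---|
| 2 | 21 |
| 3 | 17 |
| 4 | 14 |
| 5 | 13 |
| 6 | 11 |

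At m = 6 and N = 11, λ = 0.33² × 11 × 6 / 0.50 = 14.37 with 5 and 50 df, and power is 0.802. Then 11/0.90 = 12.2, rounded up to 13. The stated figures are reproduced with six measurements, which fits 3 conditions × 2 times. The 2 × 2 layout described in section 2.10 has four measurements and would need 14 (power 0.68 at 11 and 0.77 at 13). Since m is not stated, that the control was counted is an inference. The point does not depend on it.

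**4. Precision of either contrast**

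Inputs: n = 13 and r = 0.50 from section 2.3. Assumed: r applies to every pair of the six measurements, with a common SD.

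- Variance of one change = 2(1 − r) = 1 SD².
- Covariance of two changes = r − r − r + r = 0.
- Variance of the difference of two changes = 4(1 − r) = 2 SD².
- SE = √(2/13) = 0.392 SD.
- 95% half-width = 2.179 (t, 12 df) × 0.392 = about 0.85 SD.

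The result is the same for video minus control and for video minus live. The range under other assumptions is:

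| n | r | SE (SD) | 95% half-width (SD) |
|---|---|---|---|
| 13 | 0.30 | √(2.8/13) = 0.464 | 2.179 × 0.464 = 1.01 |
| 13 | 0.50 | 0.392 | 0.85 |
| 13 | 0.70 | √(1.2/13) = 0.304 | 2.179 × 0.304 = 0.66 |
| 11 | 0.50 | √(2/11) = 0.426 | 2.228 × 0.426 = 0.95 |

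With Bonferroni over three pairwise contrasts (α = 0.05/3 = 0.0167), n = 13 and r = 0.50, the half-width is 2.779 × 0.392 = 1.09 SD.

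**The case against.** The strongest reply is that section 2.9 does not shut the control out. It refers back to measurements that section 2.7 also takes on the control occasion, and it adds the response of completers. This is fair as far as it goes. A reader might infer that the plan deliberately judges the video against the live class alone, and the text does not go that far. But the control is still attached to no contrast in either 2.9 or 2.10.

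A second reply is that whether the video works belongs to the primary question on the acute effects of the programme, which is given in both formats, and that live versus video is then the natural secondary comparison. The reading is possible. It moves the problem without solving it, because section 2.10 names no comparison with control for the primary question either.

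A third reply is that adding control to the ANOVA in 2.10 would supply video versus control through the Bonferroni post hoc tests. That is largely right, and it forms half of the fix. A reader might infer that the defect would survive such a change. What would survive is mainly the wording of 2.9, which should say which contrast answers the question.

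The fourth reply limits the fix. Section 2.5 randomises only which of the two formats comes first. Control is a third occasion with no randomised position described, so video minus control may carry period and practice effects that the randomised live-versus-video contrast is better protected against. Section 2.6 also places the video class in the laboratory, with a carer and research staff present. Both limits stand and should be reported with the result.

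**Conclusion.** The point holds as a mismatch between the secondary question and the contrast named for it. The expected null difference between formats could not show that the video works, and uncontrolled pre-to-post change within the video condition is only a partial answer. This follows from the text and from the algebra, and it rests on no assumed effect size.

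The size is a matter of interpretation, not of precision. With r = 0.50 for all pairs and n = 13, either contrast has SE about 0.39 SD and 95% half-width about 0.85 SD (0.66 to 1.01 SD for r from 0.70 to 0.30). An interval that wide also means that a non-significant difference between formats would be weak evidence that they are equal.

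Two stronger readings should be resisted. A reader might infer that video minus control would be a clean answer for people at home. It would not, because the control's place in the order is not described as randomised and the video class is given on site. A reader might also infer that the change brings a gain in power. The documents give no effect size for either contrast, so they support no such comparison.

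The change is worth making because the data are already planned. The objective is secondary, and the weight of the point should reflect that.

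**What to change.** - **Section 2.10:** include control as a third level of condition (three conditions × two times).
- **Section 2.9:** name the asynchronous-minus-control difference in pre-to-post change, with its 95% CI, as the contrast for the video's effectiveness. Keep synchronous versus asynchronous as a separate comparison, identified as the randomised one.
- **Limits to state with the result:** the control occasion is not described as part of the randomised order, so period and practice effects are possible; and the video class is delivered in the laboratory, so the contrast does not directly show effectiveness at home.

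The cost is a few sentences and one more reported contrast from data already planned, with no extra participants or visits. If that contrast is Bonferroni-adjusted with the other pairwise comparisons, its power falls and its interval widens, from about 0.85 to about 1.09 SD under the assumptions above.
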